## Abstract

**Background:**

The Paris and Nice terrorist attacks affected a thousand of trauma victims and first-line responders. Because there were concerns that this might represent the first of several attacks, there was a need to quickly enhance the local capacities to treat a large number of individuals suffering from trauma-related disorders. Since Reconsolidation Therapy (RT) is brief, relatively easy to learn, well tolerated and effective, it appeared as the ideal first-line treatment to teach to clinicians in this context.

**Methods:**

This study protocol is a two-arm non-randomized, multicenter controlled trial, comparing RT to treatment as usual for the treatment of trauma-related disorders. RT consists of actively recalling one’s traumatic event under the influence of the ß-blocker propranolol, once a week, for 10–25 min with a therapist, over 6 consecutive weeks. This protocol evaluates the feasibility, effectiveness, and cost-utility of implementing RT as part of a large multi-center (*N* = 400) pragmatic trial with a one-year follow-up.

**Discussion:**

Paris MEM is the largest trial to date assessing the efficiency of RT in the aftermath of a large-scale man-made disaster. RT could possibly reinforce the therapeutic arsenal for the treatment of patients suffering from trauma-related disorders, not only for communities in western countries but also worldwide for terror- or disaster-stricken communities.

**Trial registration:**

Clinical Trials (ClinicalTrials.gov). June 3, 2016. NCT02789982.

## Background

The terrorist attacks that struck France in 2015 and 2016 were the most devastating and deadly events to occur on its territory since WWII, with a thousand of individuals physically or psychologically injured by the attacks according to official numbers [1]. Past research suggest that up to 20% of individuals exposed to this type of event develop posttraumatic stress disorder (PTSD) [2]. PTSD’s core symptoms are: re-experiencing, avoidance, alterations in mood and cognition, and hyperarousal [3]. Epidemiological studies indicate a median time of 3 years before remission when the disorder is treated, and of 5 years when left untreated, with a significant proportion of unremitted individuals 10 years after trauma exposure [2]. PTSD is also frequently comorbid with major depression (48–55%), dysthymia (21–23%), generalized anxiety disorder (15–17%), social phobia (28%), specific phobia (29–31%), panic disorder (7–13%), alcohol abuse (28–52%), and substance abuse (27–35%) [2, 4, 5]. Given the magnitude of the events that took place in France in 2015–16, and considering the poor prognosis of PTSD from a human suffering perspective, in the aftermath of the terrorist attacks there was an urgent need to quickly enhance the treatment resources in France. There were also fears that this attack might be the first one of a series of such events. We also reasoned that this massive terrorist attack might serve as a learning experience and, if successful, the treatment strategy deployed in Paris and Nice might serve in similar circumstances elsewhere in the future.

In order to address this unexpected plight, the research center of the Douglas Mental Health University Institute (Canada) and the public healthcare system of Paris (*Assistance Publique – Hôpitaux de Paris [AP-HP], University Hospitals of Ile de France, France*) worked together to build an innovative care proposition, named Paris MEM (shorthand for ‘*Paris, Mémoire Vive’*). The aims of this project were: (a) to quickly train a group of at least 40 mental health professionals on 20 sites in using Reconsolidation Therapy (RT), as developed by [name] [6]; (b) to offer to patients, in addition to the already existing care propositions (i.e., treatment as usual), a brief innovative first line treatment for PTSD; (c) to assess the effectiveness and the cost-utility of RT versus treatment as usual (TAU), and (d) to enhance the overall preparedness in France, in the event of subsequent large scale terrorist attacks. In this context, RT appeared as an appealing treatment modality since it is brief, well tolerated and effective [7] and its implementation seemed relatively easy.

### Reconsolidation as an emerging therapy for PTSD

Upon retrieval, under conditions of mismatch, a consolidated memory returns to a labile state before undergoing *re*-consolidation [8–10]. A large body of animal and human research shows that a deconsolidated memory can be impaired after its reactivation using a pharmacological agent (for a review see [11, 12]), notably with the β-adrenergic receptor blocker propranolol (for a review see [13, 14]). Propranolol is a lipophilic β-blocker, widely used for a variety of diseases in the last 50 years, with very few contraindications and side effects.

In 2008, Brunet et al. [15] were the first to show in a randomized controlled trial that long-standing traumatic memories can be durably toned down, using a treatment protocol congruent with reconsolidation theory. This intervention protocol was further refined and tested in three independent open-label trials in France, Canada and the United States [6]. The results showed a significant posttreatment decrease of PTSD symptoms, as well as at the 6-month follow-up. A recent randomized controlled trial comparing RT versus trauma reactivation + placebo confirmed such findings [7]. Reconsolidation impairment using propranolol has also been used with success in small randomized protocols for the treatment of phobias [16] and addiction [17]. In its current form, the treatment protocol for PTSD requires six once-a-week sessions of 10–25 min each with a therapist.

### Current treatments for PTSD

Psychotherapies such as Cognitive-Behavioral Therapy (CBT) and Eye Movement Desensitization and Reprocessing (EMDR), and pharmacological interventions such as the Selective Serotonin Reuptake Inhibitors (SSRIs) are all among the recommended treatment modalities for PTSD according to most guidelines [14, 18–21] and according to a Cochrane review [22]. In three randomized controlled trials (*N* = 1070), paroxetine had a significantly higher response rate than placebo ranging from 29 to 67% after 12 weeks [23–25]. The mean time for response ranged between 4 and 6 weeks. SSRIs such as paroxetine, while effective in the treatment of PTSD do not, however, offer a cure for PTSD. They must be taken daily for at least 1 year, and their side effects often lead patients to discontinue them [26]. CBT, including EMDR, comprise a variety of related approaches that have at their core exposure and/or cognitive restructuring as their main therapeutic ingredient [27, 28]. The recommended duration of individual therapy is 6–12 ninety-minutes sessions of treatment, offered once or twice weekly in an outpatient setting [14, 27]. CBT and EMDR both require strong educational and clinical backgrounds and can hardly be quickly learned in the aftermath of mass trauma. Furthermore, of the 2/3 of those who benefit from CBT at post-treatment, half of them relapse within 1 year, thereby reducing the treatment’s efficiency [29]. For all those reasons, we opted to teach RT therapy to the clinicians participating in this trial.

### Efficacy, effectiveness and efficiency

As summarized by Kim [30], efficacy is the extent to which an intervention works under ideal circumstances while effectiveness assesses whether an intervention works when provided under usual circumstances of healthcare practice. Research on effectiveness is also described as pragmatic trials (see Additional file 1) [31]. Pragmatic trials have several characteristics: 1) patient eligibility and recruitment should reflect routine practice; settings should reflect the care facilities available to a diverse population; 2) the intervention should be provided by normal staff with routine training; 3) intensity of follow-up should be similar to typical follow-up in usual care; 4) primary outcome should be directly relevant to participants and all patients should be included in the analysis of the primary outcome; 5) outcome measures are patient-centered and incorporate broad measures of health. Finally, efficiency refers to the ability to achieve a therapeutic goal using a lesser amount of time and resources than what is typically observed. Typically, efficiency is assessed by cost-utility analysis.

The co-primary aims of this pragmatic trial are to evaluate the effectiveness and the efficiency of RT therapy, as deployed in a post-terrorist attack real-world setting. Specifically, we wish to explore the feasibility of implementing in routine practice an innovative treatment for PTSD on a large scale and in a short period of time; to evaluate the acceptability of the treatment by the clinicians and from the patients’ perspectives; to assess the efficacy of RT; to determine its cost-utility compared to treatment as usual (TAU) over a 1-year period.

## Methods

### Study design

This study is a two-arm non-randomized, multicenter controlled trial, comparing RT to TAU for the treatment of trauma-related disorders. As shown in Table 1, psychometric assessments are made at baseline, after 6 weeks of treatment, as well as 3 and 12 months following study inclusion. In order to enhance external validity this study protocol is implemented into the usual healthcare system in France. Patients are offered the choice of the intervention they wish to receive. The study protocol was approved by local ethics committee (*Comité de protection des personnes* for Ile de France VI #CPP/14–16), and regulatory agencies (*Commission nationale de l’informatique et des libertés* #GPR1713292F and *Agence nationale de sécurité du medicament.* We plan to include up to 400 participants with the possibility of stopping at the end of the pre-specified inclusion period if at least 200 receiving RT are enrolled.

**Table 1 Tab1:** Overview of measures and time of assessment

Instrument	Variable	T0	Treatment sessions						T1	T2	T3
			t1	t2	t3	t4	t5	t6			
Demographics	*Sociodemographic characteristics*	X									
PCL-S	*PTSD symptom severity*	X	x	x	x	x	x	x	X	X	X
CGI	*Global patients’ condition*	*	x	x	x	x	x	x	*	*	*
MINI-S	*Diagnosis and comorbidities*	X							X	X	X
PDI	*Severity of trauma exposure*	X									
PDEQ	*Peritraumatic dissociation*	X									
WHOQOL-BREF	*Quality of life*	X							X	X	X
EQ-5D-5 L	*Quality of life*	X							X	X	X
MEDEC	*Health service utilization*	X							X	X	X
HSCL-25	*Anxiety and depressive symptoms*	X							X	X	X
QFS	*Social functioning*	X							X	X	X

*Assessed by a clinician blind to the patient’s treatment modality

T0: baseline assessment

T1: posttreatment assessment (week 7)

T2: 3-month follow-up assessment

T3: one-year follow-up assessment

PCL-S: PTSD Checklist – Specific Version, CGI: Clinical Global Impression, MINI-S: Mini International Neuropsychiatric Interview for DSM-5, PDI: Peritraumatic Distress Inventory, PDEQ: Peritraumatic Dissociative Experiences Questionnaire, WHOQOL-BREF: World Health Organization Quality of Life (brief), EQ-5D-5 L: EuroQol Questionnaire, MEDEC: Medico-Economic Questionnaire, HSCL-25: Hopkins Symptom Checklist, QFS: Social Functioning Questionnaire

### Eligibility criteria

Participants will be at least 18 years old without any upper age limit. Eligible participants must read and speak French, have a DSM-5 diagnosis of PTSD, adjustment disorder or any other specified trauma-related disorder. They must have a symptom score above 43 on the PTSD Checklist [32] and be at least moderately ill according to the Clinical Global Impression scale. They must not have a severe mental or neurological disorder (i.e., a history of bipolar or psychotic disorder, acute suicidal, homicidal, or self-injuring intentions, a traumatic brain injury in the last 5 years, an alcohol or substance dependence disorder), nor be involved in trauma-related litigation. Pregnant or breastfeeding women cannot participate in the trial for security reasons. In addition, to participate in the RT group, patients taking psychotropic medications must be on a stable dosage for at least 2 months, they must not use any medications that involve a dangerous interaction with propranolol, or have a resting heart rate inferior to 55 beats per minute, or a resting systolic blood pressure below 100 mmHg; any other contraindicating medical condition, as determined by the study physician (Fig. 1).

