### Procedure

Patients presenting with trauma-related symptoms to participating mental healthcare centers in Paris (15 centers), Lille, Fort-de-France, Poitiers and Nice (2 centers) regions are informed of the study. After the study has been fully explained to them, interested patients are asked to sign the informed consent form. The clinician then formally investigates if the study requirements are fulfilled and determines patient eligibility. Based on the patients’ choice and their eligibility for the RT group, enrolled patients are then allocated to RT or TAU. The treatment begins within 7 days of enrolment. A series of six treatment sessions are set on a once a week basis, but with a margin of 4–15 days between sessions. The patients’ general practitioner is informed about their patient’s participation in the study. The symptom assessments are conducted for both groups at baseline, and then 7, 13, and 52 weeks after study inclusion.

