### Statistical analyses

The clinical scores will be analyzed using an intention to treat (ITT) analysis: all patients allocated to RT or TAU will be analyzed. The collected data will be used to describe the 2 cohorts: the RT group and the TAU group. Variables will comprise socio-demographic parameters, duration of PTSD, psychiatric comorbidities, pre-morbid disorders, and co-prescriptions. As described above, the primary outcome for effectiveness analysis is based on the delta (T3 minus T0) of PTSD *symptom severity* (PCL-S). A first indicator will be the mean PCL- S difference between T3 and T0. The delta of EQ5D-5 L (T3 minus T0) examines efficiency from the health economic perspective.

A regression model will be used to calculate a second indicator based on the PCL-S values (t1-t6) collected between T0 and T1, allowing for the evaluation of PTSD symptoms evolution over time and its variation between individuals. A third indicator will be the rate of patients considered as treatment responders (PCL-S score < 44) at Week 7 (T1), Week 13 (T2) and Week 52 (T3). Mean and SD will also be computed for the delta of CGI score between T1 and T0. Missing data will be replaced using multiple imputation methods, provided that the data is missing at random or completely at random.

Additionally, in order to take into account the difference between the features of both cohorts (RT and TAU), we will use a propensity score of being allocated to RT to adjust the different model. For the secondary criteria, these propensity scores will be applied to the other scales used for the assessment.

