The absence of randomization could be considered a limitation. However, this choice is in line with the choice of a pragmatic trial, and ensures feasibility, considering that –based on our prior experience- we expect that patients will express a preference for RT compared to TAU. Due to the extraordinary circumstances in which this study was initiated, we felt that it would be wiser to conduct the trial by asking the study participants to express their preference toward the treatment they wished to receive (RT or TAU). Ultimately, the choice of treatment of the participants will inform us as to the treatment acceptability of RI. Additionally, recruitment would be easier using a free choice approach. As mentioned previously, a regression model highlighting the course of PTSD symptom severity over time will allow us to measure the proportion of patients responding to treatment and achieving remission. The comparison of the two treated cohorts will involve a propensity score of choosing RT treatment, in order to take into account measurable confusion factors and compensate for the absence of randomization. Also, to limit selection bias, eligibility criteria are the same for the two groups, except for contra-indications to propranolol. In the context of the terrorist attacks and ensuing mass suffering, and given the existence of efficacious treatments (SSRIs or psychotherapies), this effectiveness study is not compatible with the implementation of a placebo arm. A placebo controlled trial was recently published and showed the efficacy of RT versus placebo [7].

The absence of blinding is another limitation in our study. Neither the patients nor the assessors are blind for the primary criterion of assessment (PCL-S score), as is always the case in psychotherapy research. A single-blind pre/post evaluation is conducted for the CGI criterion, with the same rater who does not participate in the patient’s care. In addition, because the main outcome is a PTSD symptom self-report –and not a clinician-based interview- there is no interviewer bias.

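### RT-only entry criteria leave RT-ineligible patients in TAU with no chance of RT, so the propensity-adjusted RT versus TAU comparison of all allocated patients is open to bias

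*Protocol article*

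**What the plan says.** The Eligibility criteria section of the protocol article first gives conditions for all participants, then conditions for RT alone:

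- "In addition, to participate in the RT group, patients taking psychotropic medications must be on a stable dosage for at least 2 months"
- no drug that interacts dangerously with the study medication
- they must not "have a resting heart rate inferior to 55 beats per minute, or a resting systolic blood pressure below 100 mmHg"
- no other contraindicating medical condition, as judged by the study physician.

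The Procedure section makes allocation depend on the patient's choice and "eligibility for the RT group, enrolled patients are then allocated to RT or TAU".

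The Statistical analyses section defines the analysis as intention to treat: "all patients allocated to RT or TAU will be analyzed". To allow for differences between the cohorts it adds adjustment by a propensity score for allocation to RT. It does not state the covariates, the way the score is used or the target population.

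The Discussion presents the score as the means of making up for the lack of randomisation. On selection bias it says that "eligibility criteria are the same for the two groups, except for contra-indications to propranolol". It expects patients to prefer RT, and says that "the choice of treatment of the participants will inform us as to the treatment acceptability" of the method.

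**The concern.** A propensity score can make two groups comparable only where each patient could have entered either group. Here some TAU patients could not have entered RT. No RT patient shares their defining feature, so the data hold no information on how such patients would have fared with RT. If that feature is related to one-year outcome, the RT versus TAU difference mixes the treatment effect with a difference in case mix. A recent change of psychotropic medication is a plausible prognostic factor; low heart rate or blood pressure is less clearly one.

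The comparison affected is the central one: PCL-S change and cost-utility against TAU, with the non-inferiority aim named in the Discussion. If RT-ineligible TAU patients do worse, RT is flattered; if they do better, RT is penalised. The expected preference for RT makes this more pressing, since the fewer eligible patients choose TAU, the larger the share of TAU made up of patients who were barred from RT.

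**Working it through.** **The plan's own figure.** The Sample size section gives a 95% CI of 27 to 33 for a mean change of 30 points in 200 patients, with an SD of 15–25. The half-width is 1.96 × SD / √200. SD 15 gives 27.92–32.08, SD 21.65 gives 27.00–33.00 and SD 25 gives 26.54–33.46. The figure reproduces within the stated SD range. It is the precision of a one-group change and this point does not affect it.

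**Inputs for the comparison.** From the documents: RT-only conditions, allocation by choice and RT eligibility, all allocated patients analysed, up to 400 patients. Not in the documents, so assumed: f, the RT-ineligible share of TAU, and d, how many PCL-S points less these patients improve than RT-eligible TAU patients. A negative d reverses the sign of everything below.

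**Closed form.** If RT eligibility plays no part in the adjustment, the TAU mean improvement is lowered by f × d, and the RT versus TAU difference is shifted by that amount.

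- f = 0.10, d = 5: 0.5 points
- f = 0.30, d = 10: 3.0 points
- any f, d = 0: no bias
- wider range, f = 0.1–0.5 and d = 3–10: 0.3 to 5.0 points.

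**How f could arise.** Suppose 10% of 400 patients (40) are RT-ineligible and 80% of the other 360 choose RT (288). TAU then has 72 + 40 = 112 patients, and f = 40/112 = 36%. Both percentages are assumptions; the example shows only that a small ineligible share of all enrolled patients can become a large share of TAU.

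**Simulation.** True RT effect 0, outcome SD 20, one measured confounder, 4,000 patients per run, 100 runs per row. Entries after f × d are bias in PCL-S points. ATE targets all patients; ATT targets patients who received RT.

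| Ineligible, of enrolled | f | d | f × d | Eligibility not in score, ATE / ATT | In score, ATE | In score, ATT | Restricted to RT-eligible |
|---|---|---|---|---|---|---|---|
| 10% | 0.23 | 5 | 1.15 | 1.32 / 1.35 | 0.59 | 0.10 | 0.10 |
| 10% | 0.24 | 10 | 2.4 | 2.58 / 2.67 | 1.11 | 0.12 | 0.11 |
| 20% | 0.41 | 5 | 2.05 | 2.14 / 2.18 | 1.06 | 0.09 | 0.08 |
| 20% | 0.41 | 10 | 4.1 | 4.19 / 4.30 | 1.94 | −0.10 | −0.08 |
| 30% | 0.54 | 5 | 2.7 | 2.69 / 2.73 | 1.43 | −0.06 | −0.06 |
| 30% | 0.54 | 10 | 5.4 | 5.50 / 5.62 | 2.99 | 0.04 | 0.02 |

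With d = 0, every adjusted estimate lies within 0.10 of zero, so the last two columns show essentially no bias. Adding eligibility to the score while weighting to all patients does not suffice: an ineligible TAU patient has propensity 0 and weight 1/(1 − 0) = 1, and so stays in the TAU mean with no RT counterpart. The bias left is about the ineligible share of all enrolled patients times d (for example 0.20 × 10 = 2.0, against 1.94 simulated).

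**The Discussion against the Eligibility criteria.** The Discussion allows one difference between groups, contra-indications to propranolol. The Eligibility criteria list psychotropic-dose stability as a separate RT condition, alongside drug interactions and contraindicating conditions. The Discussion sentence does not cover it.

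**The case against.** Much of the opposing case stands.

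- **Bias is not demonstrated.** A reader might infer that the comparison is biased. The documents give neither f nor d, so they support only that it is open to bias. The assumed 0.5–3 points is below the 5–9 points that the Sample size section calls a favourable response.
- **The propensity method is not stated.** A reader might infer that no propensity method could cope. That is wrong: matching, trimming or ATT weighting with eligibility in the score would remove these patients, as the simulation shows. Such detail may sit in an analysis plan that is not shown. What the article does fix is the allocation rule and an analysis of all allocated patients.
- **Acceptability.** A reader might infer that barred patients are counted as declining RT. The Discussion bases acceptability on patients' choice, and the Procedure section names choice and eligibility separately, so the documents do not show such a miscount.
- **Partial disclosure.** The Discussion admits the propranolol contra-indications and claims adjustment only for measurable factors. What it leaves out is the dose condition and the consequence for the score.
- **Pragmatic principle.** The section on efficacy, effectiveness and efficiency says that all patients should be in the primary outcome analysis. But RT eligibility is a baseline feature fixed before allocation; restricting on it does not break intention to treat, and the all-patient result can still be reported.
- **Data.** The text does not show that heart rate, blood pressure and interactions are checked in patients who choose TAU. The Clinicians training section lists heart rate, blood pressure and the cardiogram under adherence monitoring of RT. The eligibility flag cannot be assumed to exist.

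**Conclusion.** The point holds as a structural weakness. The entry and allocation rules together produce TAU patients with zero propensity for RT; the effect of RT versus TAU is not identified for them, and the stated analysis keeps them in. The possible bias is about f × d in either direction: 0.5–3 PCL-S points for f of 10–30% and d of 5–10 points, both assumed, and none if the RT-only conditions are unrelated to outcome. At the upper end this equals the half-width of the plan's own interval (33 − 30 = 3). The article gives no non-inferiority margin against which to scale it. Within-group change and its stated precision are unaffected. The Discussion sentence on equal eligibility is inaccurate as it stands, whatever the size of the bias.

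**What to change.** 1. Record at T0, for every enrolled patient and as far as baseline data allow, whether all RT conditions were met, including for patients who choose TAU.
2. Make RT-eligible patients the main population for the propensity-adjusted RT versus TAU comparisons of PCL-S and cost-utility. Fit the score in that set and check overlap. Alternatively, put eligibility in the score and use ATT weights or matching, so that ineligible TAU patients get zero weight. Restriction is simpler, because ineligibility predicts TAU perfectly and a logistic score would not converge cleanly.
3. Keep all allocated patients as a sensitivity analysis and describe the RT-ineligible TAU patients separately.
4. When reading acceptability, report the share choosing RT among RT-eligible patients.
5. Reconcile the Discussion sentence with the Eligibility criteria section. No entry condition needs to change for this.

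The cost is a smaller TAU group in the main comparison and one more baseline item for patients who choose TAU. If some of them were not assessed, their eligibility will be partly unknown, and the report should say how many and how they were handled.
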